### Procedure and Recruitment

We approached potential participants over the internet via social media advertisement campaigns (Facebook and Instagram). Multiple advertisement campaigns were created to promote the link to the study page. Both female and male patients and survivors of cancer of all age groups >18 years, and who have shown interest in topics related to cancer, fatigue, and cancer survivorship were targeted in the first advertising campaigns. On the basis of participant characteristics of those who showed interest (ie, clicked on the advertisement link), comparable participants (ie, look-alike audiences) were approached in subsequent advertisement campaigns.

Interested persons were directed to the landing page of the Web-based survey tool (ie, Questback) that was used for data collection. Participants were screened for eligibility, and if eligible, they received an information letter and gave digitally informed consent. Hereafter, participants completed a baseline questionnaire, after which they were randomized into the intervention or control group. Next, participants received an email with the information letter (see Multimedia Appendix 2) and their digital signed consent (see Multimedia Appendix 3). Intervention participants received a second email with a unique access code that could be used to activate the Untire app after downloading it from the app store, enabling free usage. Subsequently, participants received email invitations and reminders at 4, 8, 12, and 24 weeks to fill in the questionnaires. Once control participants completed the 12-weeks survey, they also received an email with a unique access code that could be used to activate the app after downloading it from the app store, enabling free usage. The 24-weeks follow-up assessment was used to assess maintenance of the expected decline in fatigue in the experimental group. Assessments did not last longer than 15 min.

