#### Randomization and Blinding

Participants who completed the baseline questionnaire were randomized 2:1 by the Web-based academic survey tool (ie, Questback) into the intervention and control groups. The randomization ratio was chosen for two reasons. First, we expected that intervention participants were less likely to complete the 12-weeks assessment after receiving the incentive for participation (ie, the free access to the Untire app) already at baseline, as compared with control participants who received the incentive after completing the 12-weeks measure. The 2:1 randomization increased the likelihood of a balanced number of completed 12-weeks measures. Second, in case the drop-out rate in the intervention group was higher than expected at the 12-weeks measures, it was considered convenient to have large enough numbers in the intervention group for in-depth app use analyses. Due to the character of the intervention, it was not possible to blind participants and assessors to intervention or control allocation.

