### Main Analyses

#### Does the Untire App Reduce Fatigue Significantly After 12 Weeks of App Access?

To examine a treatment effect of the app on fatigue, the data collected via Questback’s Web-based survey of fatigue severity and interference will be analyzed using General Linear Mixed Models (GLMM) for 4 repeated measures (baseline, 4 weeks, 8 weeks, and 12 weeks), and 2 groups (intervention and control), following the intention-to-treat (ITT) approach. The ITT approach refers to analyzing all participants, regardless of app use, and is the primary approach in all outcome analyses. Assumptions of linearity, homogeneity of variance as well as the normal distribution of residuals of the model will be tested. The individual measures of fatigue ratings over time (level 1) are nested within each patient (level 2). The default GLMM model without a country factor will be compared with a model with a country factor concerning the best model fit using the Bayesian information criterion.

On the basis of previous studies testing health-related apps targeting behavior [34-39], we estimated the percentage of participants that would lose interest in the app or study assessments, and, therefore, would be lost to follow-up (eg, the 12-weeks measurement), at 60%. For the data analysis, we will, therefore, employ a model that can take missing data into account (ie, GLMM). A comparison of the outcomes of the model run in the ITT approach and the outcomes of a model run among those who have completed at least the 12-week assessment (T12-completers) will demonstrate the robustness of the findings.

In addition to the model validation, we will carry out sensitivity analyses to determine whether the duration and the degree of app use are related to the degree of change in fatigue severity and interference over time. Outcomes of active users will be compared with less-active users. Active and less-active users are categorized according to the duration and degree of app use. The dose-response relationship of app use and treatment effects will be explored in a three-way interaction (time×group×activity level), using GLMM.

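### The planned comparison of the intention-to-treat model with a week-12 completer model cannot demonstrate robustness to informative drop-out, which the expected 60% loss makes the main threat

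*Protocol article*

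**What the plan says.** The section on the main fatigue analysis specifies a mixed model for four repeated measures (baseline, weeks 4, 8 and 12) in two groups, by intention to treat. It puts the share of participants who "would lose interest in the app or study assessments, and, therefore, would be lost to follow-up (eg, the 12-weeks measurement), at 60" percent. It concludes that the analysis will therefore "employ a model that can take missing data into account (ie, GLMM"). Its one check on missing outcomes is to set that model beside a model run among "those who have completed at least the 12-week assessment (T12-completers) will demonstrate the robustness of the findings". The sensitivity analyses described next in that section concern duration and degree of app use, not missing outcomes. The quality-of-life section applies the same procedure to the secondary outcome.

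Under Randomization and Blinding the protocol explains why it expects drop-out to differ by arm: "we expected that intervention participants were less likely to complete the 12-weeks assessment after receiving the incentive for participation", the free app, already at baseline, "as compared with control participants who received the incentive after completing the 12-weeks measure". Procedure and Recruitment confirms the timing: "Once control participants completed the 12-weeks survey, they also received an email with a unique access code". The allocation follows from this: "The 2:1 randomization increased the likelihood of a balanced number of completed 12-weeks measures".

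**The concern.** A likelihood-based mixed model gives a valid answer if drop-out depends only on data that were observed (missing at random). With more than half of the week-12 scores expected to be absent, the effectiveness result leans on that assumption. A robustness check should therefore ask what happens when it fails.

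The planned comparison does not ask this. Restricting to completers keeps the same week-12 scores, discards the earlier scores of those who left, and needs a stronger assumption. If people leave for reasons linked to outcomes nobody saw, both estimates can be displaced in the same direction. The text nevertheless commits the authors to reading the comparison as proof. A biased result could be labelled robust, or a sound result could be doubted because the completers disagree with it.

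**Working it through.** **Inputs from the protocol article.** Sample Size: 328 completers (164 per arm), 820 at baseline as 410 + 410, 60% drop-out, alpha 0.05, power 0.95, effect size 0.10 labelled eta-squared. Randomization and Blinding: 2:1 allocation. Results: 545 and 302 randomized. No outcome SD and no arm-specific drop-out rates are given, so effects below are in SD units and the rates are inferred.

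**1. The plan's own figure.** For a repeated-measures within-between interaction with 2 groups, 2 time points and correlation 0.5 (assumed), lambda = N × 2 × f² / (1 − 0.5). With N = 328 and f = 0.10, lambda = 328 × 2 × 0.01 / 0.5 = 13.12 and power is 0.951. So 328 is reproduced, and 328 / (1 − 0.60) = 820. This works only if 0.10 is Cohen's f; a true eta-squared of 0.10 (f = 0.333) needs N = 32. On the f reading, the implied difference in change d satisfies 13.12 = 328 × d² / 4, so d = 0.40 SD. That is the benchmark used below, and it depends on this reading.

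**2. Drop-out by arm.** Two patterns can be drawn from the document.
- Balanced completers, the stated aim of 2:1: 1 − 164/545 = 70% intervention; 1 − 164/302 = 46% control.
- Equal drop-out, as in Sample Size: 60% in both arms.

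**3. Size of a possible bias.** Let p be the drop-out rate in an arm and delta the amount by which its drop-outs are truly worse at week 12 than the model predicts. The benefit is overstated by p_I × delta_I − p_C × delta_C. The deltas are assumptions.

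| Assumed delta | 70% / 46% drop-out | 60% / 60% drop-out |
|---|---|---|
| 0.5 SD in both arms | 0.5 × (0.70 − 0.46) = 0.12 SD | 0 |
| 0.5 SD, intervention only | 0.5 × 0.70 = 0.35 SD | 0.5 × 0.60 = 0.30 SD |
| 0.2 SD, intervention only | 0.2 × 0.70 = 0.14 SD | 0.2 × 0.60 = 0.12 SD |

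Negative deltas reverse the sign, and the benefit is then understated.

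**4. Does the planned check separate sound from biased results?** A simulation used 545 versus 302 participants, four visits, correlation 0.5, monotone drop-out and 1,500 runs per scenario. Both models were fitted by maximum likelihood with unstructured covariance. Negative values favour the app.

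*Informative drop-out, true effect zero, retention 30%/54%.* Intervention participants with less improvement at week 12 were more likely to leave (log-odds b per SD), and one third of drop-outs left before week 4. Significance was judged against 1.96 times the SD of the estimates across runs.

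| b | Intention to treat | Completers | Within 0.1 SD of each other | Both falsely significant for benefit |
|---|---|---|---|---|
| 0.25 | −0.11 | −0.18 | 78% | 19% |
| 0.5 | −0.22 | −0.34 | 39% | 57% |
| 1.0 | −0.40 | −0.59 | 2% | 98% |

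With 60% drop-out in both arms, both models were falsely significant in 15%, 50% and 90%.

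*Missing at random, true effect zero, retention 30%/54%.* Drop-out depended on the last observed score (b = 1). The intention-to-treat model was unbiased (0.00) while completers showed +0.11 SD. With a true effect of −0.30 SD and the same mechanism, intention to treat gave −0.30 and completers −0.18. Intention to treat was significant in 83% of trials and both models in 39%, so in 83 − 39 = 44% a sound significant result would lack the completers' support.

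Agreement thus occurs when both are biased, and disagreement occurs when the primary model is right.

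**5. What a tipping point would report.** With an intervention-only delta, the 0.40 SD design effect disappears at 0.40/0.70 = 0.57 SD (0.40/0.60 = 0.67 SD with equal drop-out). A just-significant effect, 1.96 × √(2/164) = 0.22 SD, disappears at 0.31 SD (0.36 SD).

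**The case against.** The comparison is not worthless. The intention-to-treat model uses the earlier scores of people who left, the completer model does not, and a gap can signal selection that is visible in the observed data. A reader might infer that the two models must agree, so that the check can never fail. The simulation contradicts this: gaps averaged 0.12 SD at b = 0.5 and 0.19 SD at b = 1.0. What stands is that the check is weak and non-specific, and that it does not probe departures from missing at random.

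A reader might also infer that the bias must favour the app because those who gain nothing leave. The document does not say so. Loss of interest is attributed to participants in general. The stated reason for differential drop-out is that the incentive has already been received, not lack of benefit. Participants who improved might equally stop answering, and the protocol mentions questionnaire burden without tying it to an arm.

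The magnitudes are fragile: with equal drop-out and a common delta the bias is zero. Details of imputation commonly sit in an analysis plan that is not shown, so their absence is no fault. The protocol also names high attrition as a limitation, with reminder emails as the counter-measure. None of this rescues the clause, which states affirmatively what the comparison will prove.

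**Conclusion.** The clause is wrong and should be fixed. Agreement between the two models does not establish robustness, and disagreement does not establish bias. This conclusion needs no assumed numbers: neither model allows drop-outs to differ from what their observed data predict. It matters here because the protocol itself expects 60% loss and a different incentive structure by arm.

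The size and direction of any bias cannot be known from the document. The range of 0 to 0.35 SD for a delta of 0.5 SD rests on assumed deltas and inferred arm-specific drop-out. Set against 0.40 SD, the intervention-only values are large (0.30/0.40 = 75% and 0.35/0.40 = 88%), but that benchmark holds only if the stated 0.10 is Cohen's f. The documents do not support the stronger conclusions that the primary mixed model is invalid or that the result will be inflated.

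**What to change.** - Delete the statement that the comparison will demonstrate robustness, and report the completer model as descriptive.
- Base the robustness statement, for fatigue severity, fatigue interference and quality of life, on a multiple imputation with delta adjustment. Let delta vary separately by arm and in both directions, and report the tipping point at which the conclusion changes.
- Include the collected baseline and interim scores (fatigue, depression, sleep, pain interference, catastrophizing) as auxiliary variables in the imputation. Table 2 schedules them at weeks 0, 4, 8 and 12 in both arms.
- State the range of deltas considered plausible before the comparison by arm is examined. If that is no longer possible, label the analysis post hoc.
- Control-based imputation for intervention drop-outs is optional. Missing a survey is not the same as stopping the app, whose use is logged separately.

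The cost is a little programming on data already held. The downside is that the conclusion may have to be more cautious.

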**Methods:**

The Untire app study is a waiting list RCT targeting cancer patients and survivors who experience moderate to severe fatigue via social media (Facebook and Instagram) across 4 English-speaking countries (Australia, Canada, the United Kingdom, and the United States). The Untire app includes psychoeducation and exercises concerning energy conservation, activity management, optimizing restful sleep, mindfulness-based stress reduction, psychosocial support, cognitive behavioral therapy, and physical activity. After randomization, participants in the intervention group could access the Untire app immediately, whereas control participants had no access to the Untire app until the primary follow-up assessment at 12 weeks. Participants completed questionnaires at baseline before randomization and after 4, 8, 12, and 24 weeks. The study outcomes are fatigue (primary) and quality of life (QoL; secondary). Potential moderators and mediators of the hypothesized treatment effect on levels of fatigue and QoL were also assessed. Link clicks and app activation are used to assess reach and uptake, respectively. Log data are used to explore the characteristics of app use. Sample size calculations for the primary outcome showed that we needed to include 164 participants with complete 12-week measures both in the intervention and the control groups. The intention-to-treat approach is used in the primary analyses, which refers to analyzing all participants regardless of their app use.

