#### In-App Log Data

Log data are used to explore the characteristics of app use. Once participants activated their unique access code and gave consent to the privacy terms in the Untire app, participants were registered, and their log data were stored anonymously. Log data are automatically stored data about the activities and assessments (ie, Quick scans and the Vase of Energy) that participants perform, and registers the date on which activities and assessments were performed. App use can be described based on (1) the duration of app use in days and (2) the degree of app use. Log data will indicate the first, and the last time a participant completed an activity and the number of days between the first and last activity will be used as a proxy for the duration of app use. The number of completed activities will be counted and will be used as a proxy for the degree of app use, with a higher number of completed activities indicating more app use.

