### Sample Size

Sample size calculations for the primary outcome of fatigue showed that we needed to include 164 participants with complete 12-weeks measures in the intervention and the control group (total N=328) to detect a between-group difference in change from baseline to 12 weeks with a minimal effect size of η^2^=0.10 (alpha=.05, 1−beta=.95). The sample size was calculated using the simplest between/within-group comparison (F tests—repeated measures analysis of variance [with within-between interaction]) in G*Power 3.1. With the inclusion of 820 participants (410 intervention participants; 410 control participants) and an estimated drop-out of (492/820) 60.0%, 164 participants are expected to remain in the intervention and 164 in the control group at the 12-week primary outcome measurement. The total baseline completer sample size of N=820 can be taken as a conservative upper bound as the final analyzes will be carried out using GLMM. GLMM takes more information into account and, thus, requires a smaller sample size given the same power.

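### The exploratory dose-response analysis cuts logged app use into active and less-active users, which hides the shape of any relation and, if the relation is graded, discards information

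*Protocol article*

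**What the plan says.** In the protocol article, the section In-App Log Data defines two measures of use. For duration, "the number of days between the first and last activity will be used as a proxy for the duration of app use". For degree, "The number of completed activities will be counted and will be used as a proxy for the degree of app use". Both are counts.

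The main analysis section on fatigue after 12 weeks then plans "sensitivity analyses to determine whether the duration and the degree of app use are related to the degree of change in fatigue severity and interference". The stated method is a comparison of two named groups: "Outcomes of active users will be compared with less-active users", with the rule "Active and less-active users are categorized according to the duration and degree of app use". The model follows: "The dose-response relationship of app use and treatment effects will be explored in a three-way interaction (time×group×activity level), using GLMM".

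The article gives no cut-off, split proportion, distribution of use or expected strength of relation. It describes no model of fatigue change with app use on its full scale. The section Randomization and Blinding names in-depth analysis of app use as the second of two reasons for 2:1 allocation.

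**The concern.** The question is graded (does more use go with more change?) and the data are graded, but the stated comparison has two levels. Everyone within a level is treated as having had the same dose. Two levels give one difference. They cannot separate a steady gradient from a plateau or a threshold, and they yield no estimate per activity or per day. The result also depends on where the cut is placed. The article gives no clinical or guideline reason for a cut, and the instruction to use the app at least weekly is not tied to the categories.

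At stake is the app-use question itself. A real gradient is more likely to be missed, and what is found is harder to use for improving the app, which the Conclusions name as a practical aim.

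**Working it through.** **The plan's own figures.** The only sample size in the article is for the primary comparison. In Sample Size, 820 × (1 − 0.60) = 328, and 410 × 0.40 = 164 per arm. Results reports 545 randomised to the intervention, so 40% retention gives 545 × 0.40 = 218. No power figure is given for the app-use analysis, so there is none to reproduce. Alpha of 0.05 is taken from Sample Size ("alpha=.05, 1−beta=.95").

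**Information lost by a two-group split.** The share lost for a linear relation is 1 − corr(X, split)². For normal X with a proportion p above cut c, the share kept is φ(c)² / [p(1 − p)].

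- 50/50: 0.3989² / 0.25 = 0.637 kept, 36.3% lost (1 − 2/π)
- 30/70: 0.576 kept, 42.4% lost
- 20/80: 0.490 kept, 51.0% lost
- 10/90: 0.342 kept, 65.8% lost

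**Other distributions of use** (assumed and simulated; relation linear in X):

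| Distribution | Loss at median split |
|---|---|
| U-shaped, beta(0.5, 0.5) | 19% |
| Uniform | 25% |
| Bimodal, ±1.5 SD | 25% |
| Exponential | 52% |
| Negative binomial, shape 0.5, mean 20 | 62% |
| Lognormal, log SD 1 | 73% |

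The cut matters too. The U-shaped case loses about 79% at 10/90, while the exponential loses about 35% at its best cut (20/80).

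**With non-users set to zero.** Assume 20% to 50% non-users and lognormal counts among users (log mean 1.5 to 3, log SD 1). The median-split loss is then about 17% to 37% if the relation is linear in log(1 + count), and about 70% to 78% if it is linear in the raw count. The low end moves by a few points with the assumed shape: about 15% with half non-users and log mean 3.

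**No-loss case.** If fatigue change depends on use only through a step exactly at the cut, the split loses nothing.

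**Power illustration.** Assume a correlation r = 0.22 between use and 12-week change (a chosen value; the article gives none), normal use and a two-sided alpha of 0.05. By Fisher's z, power ≈ Φ(atanh(r)·√(n − 3) − 1.960). A median split multiplies r by √0.637 = 0.798, so 0.22 becomes 0.1755.

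- n=164, full scale: 0.2237 × 12.689 = 2.838, power 81%
- n=164, median split: 0.1774 × 12.689 = 2.251, power 61%
- n=218, full scale: 0.2237 × 14.663 = 3.279, power 91%
- n=218, median split: 0.1774 × 14.663 = 2.601, power 74%

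At n=164 the drop is 15 points at r=0.15 (48% to 33%) and 10 points at r=0.30 (98% to 87%).

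**The case against.** The strongest reply is that this is a condensed article. Cut-offs, the coding of activity level and any companion model with continuous use could sit in a full plan. The categorising sentence could also mean that each measure is categorised separately, so a reader who infers that both are forced into a single label goes beyond the text. This limits the wording. It does not remove the point: two named categories is the natural reading, the article states this as its method, and no cut-off specified elsewhere would cure the split.

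A reader might also infer that 36% is the minimum loss. It is not. It needs a normal exposure and a linear relation, and app-use counts with many non-users are unlikely to be normal. The loss can be well below or well above it.

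The power figures are likewise only an illustration. The value r=0.22 is assumed, and the planned model uses four repeated measures and tolerates missing data, whereas the calculation is a completers' correlation. This objection stands as to size, not direction.

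Finally, the analysis is labelled sensitivity and exploratory, and intention-to-treat is primary for all outcome analyses. Days active and number of activities are to be reported anyway in the uptake and usage section. This stands in full and keeps the consequence small.

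**Conclusion.** The point holds as a cheap improvement to an exploratory analysis. The plan holds two full-scale measures of use and asks a graded question, but states a two-group comparison that cannot show a dose-response shape or an effect per unit of use. For a graded relation the information loss is about 36% under normality, linearity and a median split, and roughly 17% to 80% across the other assumptions tried. It is zero for a threshold at the cut. The article supplies none of these inputs, so the size is a range under stated assumptions.

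A reader might infer that the trial's effectiveness conclusion is weakened. The article does not support that, because the primary intention-to-treat comparison does not use app-use categories. A separate matter is that "control participants had no access to the Untire app until the primary follow-up assessment at 12 weeks", so activity level is zero or undefined for controls in the three-way interaction. Changing the scale of use would not by itself settle that.

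**What to change.** In the main analysis section, replace the active/less-active categories in the dose-response model with the logged quantities on their full scale, within the intervention arm. Fit time × log(1 + completed activities) and, in a separate model, time × days of use. Enter participants who never activated the app as zero, and add a spline or quadratic term to check the shape. Report the change in fatigue per doubling of (1 + completed activities) and per day of use. Keep the active/less-active comparison as a descriptive table.

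The cost is a few sentences and a re-specified exploratory model that no longer carries the group term. It needs no new data and no extra participants. There are two downsides. A functional form must be chosen, which the shape check addresses. Days between first and last activity also remains only a proxy for duration: two activities 80 days apart score 80 days.

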#### What Are the Reach, Costs of Online Recruitment, and What Is the Uptake and Usage of the Untire App (Study)?

To explore the number of participants reached using Web-based social media campaigns, we will use the number of Web-based advertisement link clicks, leading to the study landing page. To determine the costs of recruitment, the number of link clicks will be compared with the budget spent on social media campaigns. We will calculate the total costs of recruitment, the costs per person who clicked the link, and the costs per person that completed the baseline (study) assessment. To examine how many participants completed the assessments, activated the app, and used the app in the first 12 weeks of the study, percentages and count data will be used. Log data will indicate how many participants activated their unique access code, the number of days a participant has been active in the app, and the number of activities performed.

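### The exploratory time×group×activity model cannot be estimated over weeks 0 to 12, because no control has app use; what can be fitted is a non-randomised contrast within the intervention arm

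*Protocol article*

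**What the plan says.** In the protocol article, the main analysis of fatigue is a mixed model for "4 repeated measures (baseline, 4 weeks, 8 weeks, and 12 weeks), and 2 groups (intervention and control"), with intention-to-treat as the primary approach. The last paragraph of the same section adds what it calls sensitivity analyses of app use: "Outcomes of active users will be compared with less-active users", with the grouping described as "Active and less-active users are categorized according to the duration and degree of app use". It then states: "The dose-response relationship of app use and treatment effects will be explored in a three-way interaction (time×group×activity level), using GLMM".

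Three other places decide who can have an activity level:

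- The abstract (Methods) says that "control participants had no access to the Untire app until the primary follow-up assessment at 12 weeks".
- Procedure and Recruitment gives the timing: "Once control participants completed the 12-weeks survey, they also received an email with a unique access code".
- In-App Log Data says that logging begins only after a participant has activated the code and accepted the privacy terms.

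The article gives no rule for assigning an activity level to controls. The section on quality of life adopts the same analytic procedure, so the term would carry over to that outcome.

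**The concern.** A three-way interaction asks whether the group difference in change over time varies with activity level. To answer that, both activity levels must occur in both groups. Activity here is use of an app that controls could not open during the modelled period, so the control side of the comparison is empty.

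Software may still produce output by dropping redundant columns. A reader would take that output as evidence that the treatment effect grows with use. It would in fact compare people who chose to use the app more with people who chose to use it less, all in one arm. Anything that drives both use and recovery would appear as a dose-response. App use is not marginal to the design: Randomization and Blinding gives in-depth analysis of app use as one of two reasons for the 2:1 allocation.

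**Working it through.** **Inputs.** From Main Analyses: 4 time points, 2 groups, 2 activity levels. From the abstract, Procedure and Recruitment, and In-App Log Data: controls have no app use from week 0 to week 12. From Results: 545 participants were allocated to the intervention. From Main Analyses: 60% loss expected by week 12. The plan states no figure for this analysis, so there is none to reproduce.

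**Step 1: can the term be estimated?** Let T be the intercept plus three time indicators (4 columns), g = 1 for intervention, and a = 1 for active. The full model has the blocks T, g·T, a·T and g·a·T, which is 4 × 4 = 16 columns.

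- *Controls coded a = 0.* Then a = 1 occurs only where g = 1, so g·a = a in every row. The block g·a·T (one activity×group column and three time×activity×group columns) equals the block a·T. The occupied cells are control, less-active and active, at 4 times each: 3 × 4 = 12. The computed rank is 12 of 16, and the three-way term has no estimable degrees of freedom.
- *Controls coded missing.* All control rows drop out, g is constant, and 2 × 4 = 8 cells remain. The model contains no group comparison.
- *For comparison, controls at both activity levels.* The rank is 16 of 16. The design causes the problem, not the model class.

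A three-level factor (control, less-active, active)×time has 3 × 4 = 12 parameters and matches the occupied cells exactly.

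**Step 2: what does the remaining contrast measure?** The Intervention section lets participants set their own pace and choose their modules, so activity is self-selected after randomisation. Suppose the app has no effect. Let y be the standardised change that would occur anyway and u the standardised use, bivariate normal with correlation r. With a split of u at its median, the expected gap in y between active and less-active users is

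2 × √(2/π) × r = 1.596 r.

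A simulation of this set-up (2,000 runs per row and sample size, true app effect zero) gave the following. The second sample size is 0.40 × 545 = 218, the number left after 60% loss.

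| Assumed r | Formula gap (SD of change) | Simulated gap, n = 545 | p < 0.05, n = 545 | p < 0.05, n = 218 |
|---|---|---|---|---|
| 0 | 0 | 0.00 | 4% | 4% |
| 0.1 | 0.16 | 0.16 | 43% | 23% |
| 0.2 | 0.32 | 0.32 | 97% | 66% |
| 0.3 | 0.48 | 0.48 | 100% | 95% |

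The values of r and the median split are assumptions; the documents give neither. A negative r reverses the sign: if people who recover stop using the app, a real benefit of use would be masked.

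**The case against.** The analysis is exploratory. The article says it will be explored, asks only whether use is related to change, and keeps intention-to-treat as the primary approach. None of the listed aims depends on the three-way term. This stands, and it limits the weight of the point.

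A reader might infer that the model will crash, or that the trial's conclusion is at risk. The documents support neither. Dropping the redundant columns leaves a valid 12-parameter model, and the primary result does not use activity at all.

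A reader might set the spurious gap against the effect the trial was sized to detect. The Sample Size section gives only η²=0.10. Turning that into SDs of change needs a different reading of the effect size and a within-person correlation that the article does not state, so the comparison has no documented benchmark.

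A reader might also see a contradiction between the two usage measures, "the number of days between the first and last activity will be used as a proxy for the duration of app use" and "the number of days a participant has been active in the app". The first is openly a proxy, based on completed activities and paired with a count of them. The second describes uptake, in a section that already looks at the first 12 weeks. Two measures for two purposes do not conflict, and exact cut-offs may be left to the analysis plan.

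Controls could in principle be classified by their use after week 12, which would make the term estimable. The article does not plan this. It would rest on a different exposure period and cover only controls who completed the 12-week survey.

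**Conclusion.** The point holds for the specified term. On weeks 0 to 12 the three-way interaction is aliased with time×activity (rank 12 of 16). This follows from the design and needs no numerical assumption. The part that can be estimated is a self-selected contrast within the intervention arm. Its possible bias, about 1.6×r SD of change for a median split, depends wholly on an assumed r and can run in either direction. It shows that a modest correlation would be enough to mislead, not that such a correlation exists in this trial.

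The sensitivity label is also wrong: the analysis asks a different question from the intention-to-treat estimate and does not test its robustness. The comparison with participants who completed week 12, described in the same section, is the one meant for that purpose. This should be fixed, but it does not threaten the primary analysis.

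**What to change.** Replace the three-way term with either activity×time within the intervention arm, or a three-level factor (control, less-active, active)×time. Count intervention participants who never activated their code as zero use, so that they are not lost for want of log data. Base activity on the first 12 weeks only. Move the analysis out of the sensitivity analyses, do not call it a dose-response of the treatment effect, and report it as a non-randomised association without causal wording. In the three-level version, neither user group's comparison with control is randomised, and the text should say so. Apply the same change to quality of life.

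Optionally, add a complier average causal effect for code activation, with randomised allocation as the instrument. Activation is a yes/no event, so no use threshold has to be chosen now that data collection has ended. The exclusion restriction must be stated. It is open to doubt in an unblinded waiting-list trial, whose own limitations section concedes that controls may wait to change. Missing 12-week outcomes must be handled explicitly, given the 60% loss expected. This estimate also answers a different question from the association with use.

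The cost is revised wording and modest programming on data already collected. The optional estimate adds a wider interval and an assumption that cannot be tested.
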